#### Secondary outcome assessment

The secondary outcome is change between baseline and the end of treatment in the TCM syndrome quantitative score [23], VAS scores [27] and time of onset of pain relief after administration of the drug. The VAS scores range from 0 mm to 100 mm, and it is widely used for clinical evaluation of the degree of pain. The time when the VAS score was reduced by at least 10 mm for the first time after administration of the drug was recorded, namely the time of onset of pain relief.

### Sample size estimation

Our study was designed as a non-inferiority trial and sample size calculations are based on the primary outcome measurement. First, the minimal clinically important difference in WOMAC scales in KOA is estimated from previous studies [28] as 15.50 points. Second, we assume that based on previous literature [29], the square deviation of the WOMAC score is 318.88. For power of 80% and an alpha value of 2.5% (two-tailed), the sample size is calculated using the following formula:$$ n=\frac{\frac{4}{3}{\left({u}_{\upalpha}+{u}_{\beta}\right)}^2{\upsigma}^2}{{\left(\varDelta -\updelta \right)}^2}\ \left({u}_{\upalpha}=1.6449,\kern0.5em {u}_{\beta }=1.2816\right) $$

Thus, we obtained the sample size of 1600 patients for this trial; allowing for a conservative 20% dropout rate, the total sample size was set at 2000 patients (1500 in the Tong-luo Qu-tong plaster group).

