**Discussion:**

This study will provide reliable evidence of the effectiveness and safety of Tong-luo Qutong plaster in patients with KOA. If the results are favorable, it is expected that the patients with KOA will benefit from this study, many patients may have a good alternative treatment for KOA.

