## Methods and designs

### Trial design

This will be a randomized, double-blind, parallel positive controlled, multicenter clinical trial; a non-inferiority trial design was adopted. With the unceasing development of medical technology, there are increasing numbers of positive drugs with the exact curative effect in clinical treatments. Once a treatment has been established as effective, it would be unethical to undertake placebo-controlled trials [17], which has led to more widespread application of clinical non-inferiority trials over recent decades [18, 19]. A non-inferiority trial design could be a better alternative to indirectly show the efficacy of a new treatment [20].

Each participant will sign an informed consent form (ICF) before the research is performed. A total of 11 medical institutions are involved in the study; subjects will be enrolled at eleven hospitals, including Longhua Hospital Affiliated to Shanghai University of TCM, The first Affiliated hospital of Guangzhou University of TCM, Zhengzhou Central Hospital, Suzhou Hospital of TCM, Luoyang Orthopaedics-Traumatological Hospital, Xiangyang First People’s Hospital, Liaoning Hospital of TCM, The Second Hospital of Nanjing Medical University, The Fourth Central Hospital of Tianjing, Changchun University of TCM and Shandong University of TCM. Longhua Hospital Affiliated to Shanghai University of TCM takes charge of the total clinical scheme design. The study protocol has been approved by the ethics committee of Shanghai University of TCM on the use of human subjects for research (approval number 2016LCSY097); each participating center has conducted ethical filing and has ethical approval from the main central hospital.

The study phases are shown in Fig. 1. A total of 2000 patients with KOA will be recruited and randomly allocated into the experimental group (*n* = 1500) or the control group (*n* = 500); each patient will undergo a 2-week treatment with herbal patches for one session per day. A flow chart of trial participation is provided in Fig. 2. Efficacy and safety data will be collected throughout the whole study.

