### Randomization

This study is designed as a randomized, double-blind, parallel positive drug controlled, multicenter clinical trial. A total of 2000 eligible participants will be randomized (3:1) using a stratified-block randomization method based on the disease and the center to two treatment groups: the experimental group (Tong-luo Qu-tong group) and the control group (Qi-zheng Xiaotong group). A number of previous clinical studies also had adopted unequal allocation-ratio designs, which allows the minimization of potentially unethical exposure of patients to a placebo [30–32]. However, our study lacked a placebo group, which is different from previous studies. Based on the above, we drew up an appropriate unequal allocation ratio. All eligible patients were assigned in a 3:1 ratio (Tong-luo Qu-tong plaster group: Qi-zheng Xiao-tong plaster group) by a stratified-block randomization method; the study design ensured a greater number of patients undergoing Tong-luo Qu-tong plaster exposure by employing an unequal allocation ratio. This provided better safety assessment and greater exposure for testing the efficacy of Tong-luo Qu-tong plaster in this randomized controlled clinical trial, to generate good evidence to answer the trial research question. SAS statistical software 9.2 (SAS Institute, Cary, NC, USA) will be used to generate a randomization scheme based on the PROC PLAN function, which will be used to link the patient to a treatment arm and will specify a unique medication number for the first package of study drug to be dispensed to the patient.

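### The non-inferiority margin is never stated: the only difference given, an MCID of 15.50 WOMAC points, is too wide to be one and does not yield the planned 1600, which implies about 3 points

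*Protocol article*

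**What the plan says.** The section Sample size estimation opens with "Our study was designed as a non-inferiority trial and sample size calculations are based on the primary outcome measurement". It then gives two numerical inputs: "the minimal clinically important difference in WOMAC scales in KOA is estimated from previous studies [28] as 15.50 points", and a variance, "the square deviation of the WOMAC score is 318.88". The formula divides by (Δ−δ)². Neither Δ nor δ is defined or valued, and 15.50 is never called the margin. No other between-group WOMAC difference appears in the article. The result is 1600 patients, and then "allowing for a conservative 20% dropout rate, the total sample size was set at 2000 patients", allocated 3:1.

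Two other statements show what the comparison is meant to establish. Under Trial design, the absence of a placebo arm is defended on the ground that "Once a treatment has been established as effective, it would be unethical to undertake placebo-controlled trials", and non-inferiority is presented as an indirect way to show efficacy. The abstract's discussion promises: "This study will provide reliable evidence of the effectiveness and safety of Tong-luo Qutong plaster".

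**The concern.** The margin defines the hypothesis of a non-inferiority trial and fixes its size. A reader looking for it here finds only 15.50, which the article itself labels a clinically important difference. Ruling out only deficits larger than that leaves a clinically important loss possible.

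The indirect claim of efficacy also needs a margin that lies within the control's effect over placebo. The article gives no figure for that effect of the Qi-zheng Xiao-tong plaster, and there is no placebo arm to supply one. If 15.50 became the criterion, a pass could be reported as evidence of effectiveness without supporting it. If another margin was used, the reader cannot tell what a pass would mean.

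**Working it through.** **Inputs.** From Sample size estimation: difference 15.50; variance σ² = 318.88, so SD = √318.88 = 17.857; printed u_α = 1.6449 and u_β = 1.2816; 1600 evaluable; 20% dropout. From Randomization: 3:1, so 1600 splits 1200:400. From Primary outcome: WOMAC total 20 + 8 + 68 = 96.

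**Size of 15.50.** 15.50/17.857 = 0.87 SD; 15.50/96 = 16% of the scale, if the cited MCID uses that scoring.

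**Reproducing the planned size.** The dropout step works: 1600/0.8 = 2000. For 3:1 allocation the variance of the difference is σ²(1/n + 1/(3n)) = (4/3)σ²/n, so the formula's n is the control arm and the total is 4n. With Δ−δ = 15.50 and the printed z values:

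n = (4/3)(1.6449 + 1.2816)² × 318.88 / 15.50² = 3641.4/240.25 = 15.2, rounded up to 16; total 64.

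This is not 1600. The text's power and alpha (80%; 2.5%, two-tailed) also disagree with the printed z values, which correspond to 90% power and one-sided 5%. So several readings were tried. The last column inverts the formula at n = 400: Δ−δ = √[(4/3)(u_α + u_β)²σ²/400].

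| Alpha and power | Total for 15.50 | Δ−δ implied by 1600 |
|---|---|---|
| Printed z values (one-sided 5%, 90%) | 64 | 3.02 |
| One-sided 2.5%, 80% | 56 | 2.89 |
| Two-sided 2.5%, 80% | 68 | 3.18 |
| One-sided 2.5%, 90% | 76 | 3.34 |
| One-sided 5%, 80% | 44 | 2.56 |

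Reading 318.88 as an SD gives about 14,000 to 23,700 in total. No reading with 15.50 gives 1600. A difference of 3.02 with the printed z values does. Keeping Δ = 15.50 would need δ = 15.50 − 3.02 = 12.48, which is not stated.

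**Consequence if the margin were 15.50.** SE = √[318.88 × (1/400 + 1/1200)] = 1.031. At one-sided 2.5%, observed deficits up to 15.50 − 1.96 × 1.031 = 13.5 pass. The probability of passing with true deficit d is Φ((15.50 − d)/1.031 − 1.96):

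- d = 10: Φ(3.37) = 0.9996
- d = 12: Φ(1.43) = 0.92
- d = 12.5: 0.83
- d = 13.5: about 0.49
- d = 15.5: 0.025

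**Power for a 3.0-point margin, no true difference.** 3.0/1.031 = 2.910.

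- One-sided 5%: Φ(2.910 − 1.645) = 0.90
- One-sided 2.5%: Φ(2.910 − 1.960) = 0.83
- Two-sided 2.5%: Φ(2.910 − 2.241) = 0.75

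**The case against.** The article never says that 15.50 is the margin, and its own planned size argues against that: 15.50 as the whole denominator gives 64 patients. The MCID may have been one step towards a smaller margin, or δ may not be zero. The derivation may stand in the full protocol, which is not shown. This stands, and it means the pass probabilities are conditional. They also assume a confidence-bound test against the margin.

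It does not remove the problem. The article chose to print the calculation with its inputs, and those inputs contradict the stated result. That is a conflict in the text rather than detail left out of a condensed report.

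Three stronger readings might be inferred and are not supported:

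- That the trial cannot fail. Even with a 15.50 margin, a true deficit of 13.5 points passes only about half the time.
- That 15.50 exceeds the control's whole effect over placebo. The article gives no such effect, so all that can be said is that its preservation is not shown.
- That 3.0 points is the right margin. It is worked back from the sample size and has no clinical or control-effect basis of its own. Under the literal two-sided 2.5%, its power is about 75%, below the stated 80%.

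**Conclusion.** The point holds as a choice between two faults. Either 15.50 is the margin, in which case it is too wide to exclude a clinically important loss and the formula needs about 64 patients rather than 1600. Or the margin is something else, in which case the planned size implies about 3 points (2.6 to 3.3) and the document does not state it. A reader might conclude that the trial is using a 0.87 SD margin; the text does not establish that.

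The figures assume that 318.88 is the variance of the analysed outcome, improvement in WOMAC total, although the article attaches it only to the WOMAC score. They also assume that 1600 is evaluable and split 1200:400. Because the primary conclusion rests on this threshold, it needs correcting before the data are unblinded; a margin chosen afterwards would not be credible.

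**What to change.** In the protocol and analysis plan, before unblinding:

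1. Define Δ and δ and give their numerical values. Do not use the 15.50 MCID as the margin.
2. Choose a margin that the planned size supports, about 3 points if 318.88 is the right variance. Justify it clinically and against the documented effect of the Qi-zheng Xiao-tong plaster over placebo.
3. Restate the calculation with one alpha (sided), one power and matching z values, so that margin, alpha, power and 1600 evaluable agree. At the literal two-sided 2.5% and 80% power, 1600 supports 3.18 points.
4. Limit the conclusion to not worse than the Qi-zheng Xiao-tong plaster by more than Δ, unless the control's effect over placebo is documented.

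The cost is wording and the work of justifying the margin; no extra patients are needed. The downside is real: for a 3-point margin, stated power is about 75% to 90%, depending on alpha, instead of the near 100% that a 15.50 margin would give, and the trial can fail.

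### The sample size statement contradicts itself: the printed u-values do not match the stated alpha and power, and 1600 cannot be reproduced from the printed inputs

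*Protocol article*

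**What the plan says.** Everything below is in the protocol article, section Sample size estimation, unless noted.

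- Design: "Our study was designed as a non-inferiority trial and sample size calculations are based on the primary outcome measurement".
- Difference: "the minimal clinically important difference in WOMAC scales in KOA is estimated from previous studies [28] as 15.50 points". It is not called the non-inferiority margin, and no expected true difference is given.
- Variance: "the square deviation of the WOMAC score is 318.88".
- Error rates: "For power of 80% and an alpha value of 2.5% (two-tailed), the sample size is calculated using the following formula".
- Formula: n = (4/3)(uα + uβ)²σ² / (Δ − δ)², printed with uα = 1.6449 and uβ = 1.2816. Neither Δ nor δ is assigned a value.
- Result: "Thus, we obtained the sample size of 1600 patients for this trial". This is raised to 2000 for 20% dropout, 1500 of them in the experimental arm.
- Allocation (section Randomization): "All eligible patients were assigned in a 3:1 ratio".

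The Statistical analysis section names two further thresholds, two-sided 0.05 or 0.01, and does not tie either to the non-inferiority comparison.

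**The concern.** The sentence that sets alpha and power and the constants printed beside it describe different designs. The number of patients is then presented as the output of that formula, yet it is far from what the visible inputs yield.

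In a non-inferiority trial the margin decides the conclusion. A sample size calculation is normally where a reader confirms which margin, error rate and power the trial was built on. Here that check fails: the only difference printed is about five times the one that 1600 implies, and the alpha and power can be read in at least two ways.

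**Working it through.** **Inputs.** Variance σ² = 318.88 (SD 17.86), difference 15.50, printed u-values 1.6449 and 1.2816, stated power 80% and alpha 2.5%, dropout 20%, all from Sample size estimation; ratio 3:1 from Randomization. With three experimental patients per control, the factor 4/3 = 1 + 1/3 makes n the control-arm size, so the total is 4n. My assumption, because the article values neither symbol: Δ = 15.50 and δ = 0.

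**Step 1: do the u-values match the text?** Φ(1.6449) = 0.950, which is one-sided 5%. Φ(1.2816) = 0.900, which is 90% power. For 80% power uβ = 0.8416. For alpha 2.5%, uα = 2.2414 if split over two tails, or 1.9600 if one-sided. Neither printed constant fits the text. This step needs no assumption.

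**Step 2: does the formula give 1600?** With the printed u-values:

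n = (4/3)(1.6449 + 1.2816)² × 318.88 / 15.50² = (4/3)(8.564)(318.88) / 240.25 = 15.16, so 16 controls and 64 in total.

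| u-values | (uα + uβ)² | n, control arm | Total at 3:1 | After 20% dropout | Δ − δ needed for 400 controls |
|---|---|---|---|---|---|
| Printed: 1.6449, 1.2816 | 8.564 | 15.16 → 16 | 64 | 80 | 3.02 |
| One-sided 2.5%, 80%: 1.9600, 0.8416 | 7.849 | 13.89 → 14 | 56 | 70 | 2.89 |
| Two-sided 2.5%, 80%: 2.2414, 0.8416 | 9.505 | 16.82 → 17 | 68 | 85 | 3.18 |

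The stated 1600 is 1600/64 = 25 times the total from the printed u-values. The last column inverts the formula at n = 400: for the printed u-values, √[(4/3)(8.564)(318.88)/400] = 3.02. Only the dropout step reproduces: 1600/0.8 = 2000.

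**Step 3: would a simple slip explain it?**

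- 318.88 read as an SD: n = 4833 controls with the printed u-values, a total of 19,336.
- 15.50 read as 1.55: n = 1516 (printed u-values), 1389 (one-sided 2.5%, 80%) or 1682 (two-sided 2.5%, 80%). As control arms these give totals of 6064, 5560 and 6732. If n were wrongly taken as the total, the three values straddle 1600, but the nearest is about 5% away.
- n itself equal to 1600: Δ − δ would have to be 1.51, 1.44 or 1.59 for the three rows of the table.

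None of these gives 1600.

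**Step 4: which way does the error run?** With 400 controls and 1200 experimental patients, SE = √[318.88(1/400 + 1/1200)] = 1.031. For 15.50 points, 15.50/1.031 = 15.0, far above 1.96 or 2.24, so power is essentially 100%.

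**The case against.** **The formula is under-determined.** It needs Δ and δ, and the article values neither. The full protocol may hold a pair that yields 1600. This stands in part. A reader might infer that the printed inputs definitely give about 60 patients, but that holds only if Δ − δ = 15.50. It does not rescue the article, which offers 1600 as the consequence of what it has just printed. If 15.50 were the margin, 1600 would imply a true difference of about 12.3 to 12.6 points (15.50 − 3.18 and 15.50 − 2.89), also stated nowhere. The u-value mismatch is untouched, because it is a contradiction in printed text and not an omission.

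**The mismatch in u-values is small.** True on its own: the stated error rates need 7.849/8.564 = 0.92 or 9.505/8.564 = 1.11 times the printed-u sample size. It cannot account for a 25-fold gap.

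**Oversizing does no harm, and safety exposure may explain the size.** The article does defend 3:1 allocation partly by better safety assessment and more exposure to the experimental plaster. That supports the ratio and may have influenced the total, but the sample size section gives the formula as the source of 1600.

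**A reader might infer that the trial is underpowered.** The documents do not support that. Power falls towards the usual range only at differences near 3 points, a figure obtained by working backwards from N and found nowhere in the article.

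**Conclusion.** The point holds as a wrong and self-contradictory statement about the primary endpoint.

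- Certain, with no assumption: the printed constants are for one-sided 5% and 90% power, while the text says 2.5% two-tailed and 80%.
- Certain: 1600 cannot be reproduced from the figures printed.
- Conditional on Δ − δ = 15.50 and 318.88 being a variance: the total is 64, or 56 to 68 under the stated power, against 1600.
- For 15.50 points the trial is oversized, not underpowered.

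The consequence is that the stated alpha, power and difference do not describe this trial, and nobody can tell from the article which margin N was sized for. A reader might also conclude that the margin must have been about 3 points. The article does not say so; 2.9 to 3.2 is only what the arithmetic would require if 1600 came from this formula and this variance.

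**What to change.** Keep N = 2000 and rewrite the sample size paragraph in one of two ways.

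1. If 1600 came from the formula, print the prespecified Δ (non-inferiority margin) and δ (expected true difference) that were used. Give one alpha, its sidedness and one power, with the u-values that belong to them. Say that n is the control arm and the total is 4n, so that 1600 reproduces. If 15.50 was not an input, say what role it plays.
2. If 1600 was set on another basis, such as safety exposure, say so, and report the power that 1200 versus 400 evaluable patients give at the prespecified margin.

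Use the same alpha and sidedness for the non-inferiority comparison in the Statistical analysis section.

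Do not adopt a margin obtained by inverting the formula at N = 1600; nothing in the article supports such a value.

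Cost: where the margin is already on file, this is a wording correction that leaves recruitment and N unchanged, although the stated alpha and power may change. If no margin was prespecified, choosing one is a substantive design decision. Because recruitment began in September 2017, it would have to be justified independently of N and of any trial data, and documented as a change.

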### Randomization

This study is designed as a randomized, double-blind, parallel positive drug controlled, multicenter clinical trial. A total of 2000 eligible participants will be randomized (3:1) using a stratified-block randomization method based on the disease and the center to two treatment groups: the experimental group (Tong-luo Qu-tong group) and the control group (Qi-zheng Xiaotong group). A number of previous clinical studies also had adopted unequal allocation-ratio designs, which allows the minimization of potentially unethical exposure of patients to a placebo [30–32]. However, our study lacked a placebo group, which is different from previous studies. Based on the above, we drew up an appropriate unequal allocation ratio. All eligible patients were assigned in a 3:1 ratio (Tong-luo Qu-tong plaster group: Qi-zheng Xiao-tong plaster group) by a stratified-block randomization method; the study design ensured a greater number of patients undergoing Tong-luo Qu-tong plaster exposure by employing an unequal allocation ratio. This provided better safety assessment and greater exposure for testing the efficacy of Tong-luo Qu-tong plaster in this randomized controlled clinical trial, to generate good evidence to answer the trial research question. SAS statistical software 9.2 (SAS Institute, Cary, NC, USA) will be used to generate a randomization scheme based on the PROC PLAN function, which will be used to link the patient to a treatment arm and will specify a unique medication number for the first package of study drug to be dispensed to the patient.

### Drug management

In this clinical trial, one experimental drug administrator was assigned to perform drug management including drug storage, distribution, and recycling independently and kept detailed records. The whole process of drug coding and documentation is performed blinded. The drug boxes and emergency envelope contain the corresponding drug numbers, which are randomly divided between each center according to the central number for random stratification. Emergency unblinding can only happen when there a serious adverse event occurs in the study; in this event, the subject will exit the trial and the investigator will record detailed reasons for the subject’s withdrawal from the trial in the case report form.

### Statistical analysis

The statisticians and the main researchers are responsible for the statistical analysis plan. We will analyze all data with SAS 9.2 statistical software. Data sets including the full analysis set (FAS), per-protocol set (PPS) and safety set (SS), will be analyzed in terms of actual subjects, shedding cases, excluding cases, demographic and characteristics of cases, and efficacy and safety analyses will be conducted according to the intention-to-treat (ITT) principle.

Categorical data presented as frequency tables or percentages and continuous data presented as mean ± standard deviation, median, superior and inferior quartiles, minimum value and maximum value will be used to describe the characteristics of patients in both groups. The primary outcome will be compared in the two groups; categorical data will be analyzed by chi-squared test or Fisher’s exact test, and continuous data with a normal distribution will be analyzed by the *t* test or variance testing. If the data are not normally distributed or do not satisfy homogeneity of variance, they will be analyzed using the Wilcoxon rank sum test or Wilcoxon symbols test to compare the two treatment arms. A two-sided *P* value ≤0.05 or ≤0.01 will be considered statistically significant.

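### The only principle assigned to the efficacy and safety analyses is ITT, so the per-protocol set has no stated role in the non-inferiority conclusion and the safety set's role is unclear

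*Protocol article*

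**What the plan says.** The Sample size estimation section sets the framework: "Our study was designed as a non-inferiority trial and sample size calculations are based on the primary outcome measurement". It arrives at 1600 patients and, "allowing for a conservative 20% dropout rate, the total sample size was set at 2000 patients", of whom 1500 receive the experimental plaster and 500 the control.

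The Statistical analysis section has one sentence on analysis populations. Its first part reads "Data sets including the full analysis set (FAS), per-protocol set (PPS) and safety set (SS), will be analyzed", followed by a list of what the sets are described by: numbers of subjects, dropouts, exclusions, and demographic and other characteristics. Its second part reads "efficacy and safety analyses will be conducted according to the intention-to-treat (ITT) principle". No other sentence in the article links a set to the efficacy conclusion or to the safety analysis.

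The Drug management section allows emergency unblinding only for a serious adverse event. In that case "the subject will exit the trial and the investigator will record detailed reasons". The article does not say whether outcomes are still collected from that subject.

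**The concern.** In a superiority trial, ITT is usually the cautious choice, because patients who stop or do not adhere tend to dilute a difference. In a non-inferiority trial the same dilution can work in favour of the claim: a plaster that is truly worse by the margin may look closer to the comparator than it is. The usual guard is to require that FAS and PPS lead to the same conclusion. The article names a PPS, but the only principle it attaches to efficacy is ITT.

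The safety half of the sentence has a related problem. ITT counts patients by assignment, whereas a safety set is normally analysed by treatment received. Naming an SS and then placing safety under ITT leaves open which of the two governs. This matters to the design, because the Randomization section gives better safety assessment as a reason for the 3:1 allocation.

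Finally, ITT calls for outcomes on everyone randomised, while a subject unblinded under the Drug management section leaves the trial. If exit also ends data collection, the week-2 WOMAC of such subjects will be missing from the set that ITT relies on.

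**Working it through.** **Inputs from the article (Sample size estimation, Randomization)**
- Variance of WOMAC 318.88, so SD = √318.88 = 17.86.
- 1500 experimental and 500 control patients, 3:1.
- 1600 before dropout, with a 20% dropout allowance.

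**The plan's own dropout step.** 1600 / (1 − 0.20) = 2000. This reproduces. A set that lost exactly the 20% would hold 1200 + 400 = 1600.

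**Assumptions, not in the article**
- Margin M = 3.0 points. The article gives a minimal clinically important difference of 15.50 points but does not expressly call it the margin, and gives no value for the expected difference δ. A value near 3 is what the printed formula needs if its result is read as 400 controls: √[(4/3)(1.6449 + 1.2816)² × 318.88 / 400] = 3.02. Whether the 1600 follows from the stated inputs is a separate question and plays no part here.
- One-sided 2.5% test, z = 1.96.
- A share d of patients in each arm stays in the analysis and contributes no difference between arms, while the true deficit among the rest equals M.

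**Standard error with everyone kept**

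SE = √[318.88 × (1/1500 + 1/500)] = 0.922.

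**False non-inferiority**

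The observed deficit is M(1 − d), which lies dM inside the margin, so the probability of a false claim is Φ(dM/SE − 1.96).

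For M = 3.0:
- d = 0: Φ(−1.96) = 2.5%
- d = 10%: Φ(0.30/0.922 − 1.96) = Φ(−1.63) = 5.1%
- d = 20%: Φ(0.60/0.922 − 1.96) = Φ(−1.31) = 9.5%

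Range over the assumed margin:

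| Margin | d = 5% | d = 10% | d = 20% |
|---|---|---|---|
| 3.0 | 3.6% | 5.1% | 9.5% |
| 5.0 | 4.6% | 7.8% | 19.1% |
| 15.5 | 13.1% | 39.0% | 92.0% |

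The SE for 2000 is the right one here. The concern is about patients who are kept in the set, so using the SE for 1600 would remove the 20% once and then dilute for them again.

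**Power if both sets must agree** (M = 3.0, no true difference, one-sided 2.5%)
- FAS, 500 controls: Φ(3.0/0.922 − 1.96) = Φ(1.29) = 90%.
- PPS, 400 controls: SE = √[318.88 × (1/1200 + 1/400)] = 1.031, and Φ(3.0/1.031 − 1.96) = Φ(0.95) = 83%.
- Both: if the PPS is a subset of the FAS with the same effect, the two estimates correlate at 0.922/1.031 = 0.894. The bivariate normal probability of passing both at 1.29 and 0.95 is 82%.

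**The case against.** The strongest reply is that the sentence does not exclude a per-protocol analysis. PPS and SS are listed among the sets to be analysed, and their detailed roles may stand in the statistical analysis plan or the full protocol, neither of which is shown. That is fair as far as it goes. A reader might infer that efficacy will be concluded on ITT alone, or that safety will use ITT instead of the SS. The article says neither. What stands is that it does more than leave the matter open: it states one principle for both kinds of analysis, and followed as written that principle gives the PPS no part in the conclusion and conflicts with having an SS.

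A second reply is that ITT is not always anti-conservative for non-inferiority. This is correct. Imputation method, differential dropout and rescue analgesia can each move the result either way, and the article gives no missing-data method. The 20% is described as conservative and is a planning allowance, not a forecast of patients with no treatment contrast. The percentages above therefore show what could happen and are not an estimate for this trial. The 3-point margin is likewise an assumption.

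A third reply is that exit after unblinding will be rare and concerns few subjects. That also stands. A reader might infer that these subjects' outcomes are discarded, but the article does not say so: such a subject can remain in the FAS, and WOMAC is also measured at baseline and week 1. The open point is only whether the week-2 value is still sought.

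**Conclusion.** The point holds as a fault in a stated choice. In a non-inferiority trial with a 20% dropout allowance, the article puts efficacy under ITT without giving the PPS a role in the conclusion, and puts safety under the same principle although it names a safety set.

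Under the stated assumptions, an error rate of nominally 2.5% becomes about 5% at 10% dilution and about 9.5% at 20%. The figure depends strongly on the margin: at 20% dilution it runs from 9.5% for 3 points to 92% for 15.5 points. With no dilution there is no inflation. The documents do not support a claim that ITT will necessarily favour the experimental plaster, only that it can and that no guard is stated. The conflict between exit after unblinding and ITT is a minor part of the point and is not included in these figures.

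**What to change.** In the Statistical analysis section, replace the single ITT clause with three statements:
- Non-inferiority is claimed only if the confidence limit for the difference in total WOMAC improvement lies within the pre-specified margin in both the FAS and the PPS. The margin must be named as such for this rule to work.
- PPS membership is fixed at a blind review before the treatment codes are opened.
- Safety is analysed in the SS by the plaster actually received.

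Reconcile the Drug management section with ITT by stating that week-2 WOMAC and safety data are still collected, where they consent, from subjects who exit after unblinding. This concerns data collection only.

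The cost is wording and one repeated run of the same analysis. In the illustration at a 3-point margin, joint power is about 82%, slightly below the 83% of the PPS alone and below the 90% of the FAS alone. If the PPS loses only the 20% dropout, it holds the 1600 planned before dropout and no increase in sample size follows. Protocol violations beyond dropout, such as use of other traditional Chinese medicine, would take it below 1600 and reduce power further.
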